### 3.1. Study drugs

*Dihydroartemisinin piperaquine*

### DP is a fixed combination drug containing the artemisinin derivative, dihydroartemisinin, and piperaquine. Dihydroartemisinin is highly active and also the main in vivo metabolite of the drugs artesunate and artemether. Piperaquine is a bisquinoline that retains activity against chloroquine-resistant *P. falciparum*. Piperaquine replaced chloroquine as the first-line treatment for malaria in China in 1978.

### *Dosing of Dihydroartemisinin Piperaquine*

All subjects will receive DP once daily for 3 days in the morning in fixed dose tablets (40 mg dihydroartemisinin + 320 mg piperaquine) according to weight-based guidelines. A weight-based regimen consisting of a total dose of 7 and 55 mg/kg of dihydroartemisinin and piperaquine, respectively, will be given in 3 equally divided daily doses. (Appendix 6)

## 3.2. Additional medications

On day 0, patients will receive paracetamol (10mg/kg) to take every 8 hours until the resolution of fever. Patients found to have uncomplicated malaria and a concomitant illness will be treated for both and followed up according to the study protocol. For patients with anemia (Hb < 10 gm/dL), we will follow Integrated Management of Childhood Illness (IMCI) guidelines: For patients with anemia (Hb < 10 gm/dL), we will follow Integrated Management of Childhood Illness (IMCI) guidelines: anemic children will be treated with iron sulfate (100 mg daily for 2 weeks) and mebendazole (only children > 1 year of age; 250 mg age 1-2 years; 500 mg > 2 years age; treated no more frequently than every 6 months).

.

# Follow up and laboratory procedures

## *1. Follow-up schedule*

Children will be asked to return to the clinic for follow-up on days 1, 2, 3, 4 , 5, 7, 14, 21, 28, 35, 42 and any unscheduled day that they feel ill. All patients will be reimbursed the cost of their transport to and from the clinic. At enrollment, details about the location of the patient’s residence will be obtained and if a subject does not return for a scheduled clinic follow-up appointment, the study personnel shall visit them at home. Patients who return on day 1 and fail to fulfill the criteria of *P. falciparum* mono-infection with a parasite density of 2000-200,000 parasites/ul will be excluded from the study and referred to the dispensary staff for management. At each repeat visit, temperature will be measured and a focused physical examination will be performed. A finger prick blood sample will be obtained on days 2, 3,4, 5, 7, 14, 21, 28, 35, 42 and any extra day they present with a fever to repeat thick blood smears and to save blood on filter paper. Hemoglobin will be re-evaluated on day 42 or at the time of clinical treatment failure (ETF or LCF).

***2. Laboratory studies***

(i) Diagnosis of malaria

Patients who present with symptoms suggestive of malaria (fever or history of

fever) will be referred to the outpatient laboratory for a fingerprick for

screening thick blood smear (using standard Giemsa staining). Thick blood

slides will be read and counted by the laboratory technicians. The parasite

density of positive screening thick blood smears will be estimated by counting

the number of asexual parasites per 200 leukocytes, assuming a leukocyte

count of 8,000/l. Smears will be considered negative when examination of 100 high-power fields does not reveal parasites. Counts will be performed by two microscopists; discrepant readings will be resolved by a third reader. Gametocytes will be recorded as present or absent. Thin blood smears will be evaluated for parasite species.

(ii) Hemoglobin measure

Hemoglobin will measured from finger prick samples using a portable spectrophotometer (HemoCue, Ängelhom, Sweden).

(iii) In vitro test:

Patients with parasitemia of 4000/ul or more will be asked to

give 5ml of venous blood for in vitro test. The isotopic microtest or HRPII test

will be applied to determine the IC50 of piperaquine, lumefantrine, quinine

and DHA.

(iv) Molecular markers analysis:

Whenever blood will be collected, 4 drops will be placed onto filter paper,

labeled, air-dried, and stored in sealed plastic bags at ambient temperature.

Parasite DNA will subsequently be extracted using the Chelex extraction method.

We will use PCR techniques to determine new infection from recrudescence

and putative molecular markers of drug resistance. We will also analyze the

molecular markers associated with treatment failure and in vitro resistance, in particular polymorphisms in the P. falciparum pfcrt and pfmdr1 genes.

(v) Pharmacokinetic analysis

Plasma piperaquine concentrations will be determined by a validated sensitive and selective liquid chromatographic tandem mass-spectrometric (LC-MS/MS) method in the Pharmacology laboratory at Mahidol Oxford Tropical Medicine Research Unit in Bangkok.

# DATA COLLECTION AND MANAGEMENT

## *1. Data management*

All clinical data will be recorded onto standardized case record forms by study clinicians. Laboratory data will be recorded in a laboratory record book by the study laboratory technicians and then transferred to the case record forms by the study clinicians. Data will be transferred from the case record forms into a computerized database (EPI INFO 6.04) by data entry personnel and will be double entered to verify accuracy of entry. Two back-up files of the database will be stored on compact discs after each data entry session. For quality control, check programs will be written into the database to limit the entry of incorrect data and ensure entry of data into required fields.

## *2. Data quality assurance and monitoring*

All members of the study team will be educated in the study protocol prior to the onset of the trial. The study clinicians will complete case record forms at each patient visit. These forms will be reviewed by the study coordinator and site supervisors from the core facility for completeness and accuracy. For quality control of thick blood smear slide readings, expert microscopists will repeat the reading of all slides. All discrepant slide readings will be resolved based on the results of a 3rd reading. Study group meetings will be conducted by the coordinator once a week to assess progress of the study, address any difficulties, and provide performance feedback to the members of the study group. In addition members from the core facility will make regular visits to active study sites as needed.

## *3. Records*

Case record forms will be provided for each subject. Participants will be identified by their initials and study identification number on the case record form. Patient names will not be entered into the computerized database. All patient record forms will be kept in a secure filing cabinet in the study clinics. All corrections will be made on case record forms by striking through the incorrect entry with a single line and entering the correct information adjacent to it. The correction will be initialed and dated by the investigator. Any requested information that is not obtained as specified in the protocol will have an explanation noted on the case record form as to why the required information was not obtained. Additional records will be kept in the clinical and laboratory record books at the core facility in Bobo-Dioulasso. The investigators will allow all requested monitoring visits, audits or reviews.

***4. Statistical analysis and sample size***

We will search for associations between diminished drug levels of piperaquine and clinical outcomes. Available resources will allow us to study 300 patients who complete study follow-up. Estimating a 10% loss to follow-up over 42 days, we will enroll 330 patients of whom 200 will have age range from 2 to 10 years. In our recent study at the same sites, the unadjusted 42 day risk of treatment failure with DP was 7.5%. Unadjusted failures are relevant in this analysis, as low levels of piperaquine may be associated with either recrudescence or new infections emerging during the elimination phase of piperaquine. It is estimated, based on our recent study that studying 300 patients will identify 22 unadjusted treatment failures. This sample size will provide the power to identify a 3-fold difference in unadjusted treatment efficacy between the lowest piperaquine level quartile and the remainder of subjects.

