## Selection criteria

On day 0, patients with symptoms suggestive of malaria and a positive screening thick blood smear will be assessed for the following selection criteria by study physicians:

1. Not previously enrolled in this study
2. Age > 6 months
3. Weight > 5 kg
4. Fever (> 37.5ºC axillary) or history of fever in the previous 24 hours
5. Absence of any history of serious side effects to study medications
6. No evidence of a concomitant febrile illness in addition to malaria
7. Provision of informed consent and ability to participate in 42-day follow-up (patient has easy access to health unit)
8. No history of antimalarial use in the previous two weeks
9. No danger signs or evidence of severe malaria defined as:

- Unarousable coma (if after convulsion, > 30 min)
- Recent febrile convulsions (within 24 h)
- Altered consciousness (confusion, delirium, psychosis, coma)
- Lethargy
- Unable to drink or breast feed
- Vomiting everything
- Unable to stand/sit due to weakness
- Severe anemia (Hb < 5.0 gm/dL)
- Respiratory distress (labored breathing at rest)
- Jaundice

Patients fulfilling these criteria will be assigned a study number and will be referred to the laboratory. A second fingerprick blood sample will be obtained to prepare thick and thin blood smears, collect blood on filter paper, and for measurement of hemoglobin. Patients with hemoglobin levels < 5.0 gm/dL will be excluded after enrollment based on criteria for severe malaria (see above) and immediately referred back to the study physicians for appropriate care. After going to the laboratory, the subjects will be referred to the study nurse for treatment allocation and treatment with the study medications. Patients must also meet the following criterion:

1. Absence of repeated vomiting of study medications on day 0

Results of the Giemsa-stained thick and thin blood smears obtained on day 0 will not be available until after the patients have been treated and discharged from the clinic. Patients will return to the clinic on day 1 and will be excluded from the study if the following inclusion criteria are not met:

1. *P. falciparum* mono-infection
2. Parasite density 2000-200,000/ul
3. ***Treatment administration***

Administration of medications will be performed by the study nurse who will record the date and time of treatment and the patient's study number.

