Administration of all study drugs will be directly observed. If a patient fails to return to the clinic he/she will be visited at home by a home visitor who will collect information on where patients live. If patients miss their second dose of study drug, they will be excluded from the study. Study drugs given to young children will be crushed, mixed with water, and administered as slurry. Study drugs administered to older children will be given as tablets or fractions of tablets to be taken orally with a glass of water. Patients will be observed for 30 minutes to ensure that the medications are not vomited. Any patient who vomits the medication within 30 minutes of administration will be retreated with a second dose. Any patient who vomits repeatedly (> 3 times) will be excluded and referred for treatment with parenteral quinine.

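### Enrolling 330 gives at most 297 completers, not 300, because exclusions after enrolment are not counted; the effect on failures and power is small

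*Protocol*

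**What the plan says.** Protocol, Data collection and management, section 4 (Statistical analysis and sample size), starts from a resource limit: "Available resources will allow us to study 300 patients who complete study follow-up". It goes on: "Estimating a 10% loss to follow-up over 42 days, we will enroll 330 patients". From an earlier study at the same sites, "the unadjusted 42 day risk of treatment failure with DP was 7.5"%, so that "studying 300 patients will identify 22 unadjusted treatment failures". On this size it claims power for a "3-fold difference in unadjusted treatment efficacy between the lowest piperaquine level quartile and the remainder of subjects".

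The recruitment section places enrolment before the child goes to the study nurse for treatment. Later sections then remove children who are already enrolled:

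- Selection criteria: "Patients with hemoglobin levels < 5.0 gm/dL will be excluded after enrollment based on criteria for severe malaria".
- Selection criteria and Treatment administration: repeated vomiting of study drug leads to exclusion.
- Selection criteria and Follow-up schedule: children who at day 1 do not meet the mono-infection or parasite-density criterion "will be excluded from the study and referred to the dispensary staff for management".
- Treatment administration: "If patients miss their second dose of study drug, they will be excluded from the study".

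The sample-size section mentions none of these, and does not say that its 10% includes them.

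**The concern.** The expected failures and the power statement both rest on 300 completers. There are two reasons why 330 enrolled does not lead to 300.

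First, the target was apparently multiplied by 1.10 when it should have been divided by 0.90. Second, the allowance is for loss to follow-up alone, while the protocol has four further ways for an enrolled child to leave the evaluable group. Most of these are eligibility or dosing removals and would not ordinarily be called loss to follow-up.

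At stake is whether the stated numbers of completers and failures are ones that the protocol's own rules can deliver, and how far the power statement changes if they are not.

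**Working it through.** **Inputs from the protocol (sample-size section).** Target 300 completers; loss to follow-up 10%; enrolment 330; 42-day unadjusted failure risk 7.5%; 22 expected failures; 3-fold contrast of the lowest quartile against the rest.

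**Not in the protocol, so assumed here.** The post-enrolment exclusion rate e; two-sided alpha 0.05; the 3-fold contrast read as a ratio of failure risks.

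**1. Reproducing the plan's figures.**
- 300 × 1.10 = 330, which matches the stated enrolment exactly.
- 300 × 0.075 = 22.5, given as 22.

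**2. Loss to follow-up alone.**
- 330 × (1 − 0.10) = 297 completers, 3 short of 300.
- Number needed for 300: 300 / 0.90 = 333.3, so 334. The stated 330 is 4 children, or 1.2%, below this.
- Expected failures: 297 × 0.075 = 22.3, still the stated 22.

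**3. Adding exclusions after enrolment.** Completers = 330 × (1 − e) × 0.90; failures = completers × 0.075.
- e = 2%: 330 × 0.98 × 0.90 = 291; 21.8 failures.
- e = 5%: 330 × 0.95 × 0.90 = 282; 21.2 failures.
- e = 10%: 330 × 0.90 × 0.90 = 267; 20.0 failures.

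**4. Effect on power.** Let r be the failure risk in the upper three quartiles. An overall risk of 7.5% with a 3-fold ratio requires 0.25 × 3r + 0.75 × r = 1.5r = 0.075. So r = 5%, and the lowest quartile has 15%.

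The normal approximation is power = Φ[(0.10 − 1.96 × s0) / s1]. Here s0 is the pooled standard error (risk 0.075) and s1 the unpooled one (0.15 and 0.05), with group sizes N/4 and 3N/4.
- At N = 300: s0 = √[0.075 × 0.925 × (1/75 + 1/225)] = 0.0351.
- s1 = √[0.15 × 0.85/75 + 0.05 × 0.95/225] = 0.0437.
- Power = Φ(0.713) = 76.2%.

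| Completers | Assumed exclusion rate | Failures | Power, normal approximation | Power, Fisher's exact test |
|---|---|---|---|---|
| 300 | plan's target | 22.5 | 76.2% | 72.4% |
| 297 | 0% | 22.3 | 75.9% | 71.6% |
| 282 | 5% | 21.2 | 74.0% | 69.2% |
| 267 | 10% | 20.0 | 72.0% | 67.5% |

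The inflation slip alone costs 76.2 − 75.9, or about 0.4 points before rounding. An exclusion rate of 10% would cost about 4 points by the normal approximation (76.2 − 72.0) and about 5 by Fisher's test (72.4 − 67.5).

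**The case against.** The strongest case against is that little follows from this.

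- **The exclusion rate is unknown and may be low.** Parasite density is already checked on the screening smear, danger signs are assessed before haemoglobin is measured, dosing is directly observed with home visits for children who do not return, and vomiting leads to exclusion only when repeated. This stands: no particular rate can be claimed. It does not make the rate zero. Haemoglobin is measured only after a study number is assigned, the screening step describes only a thick smear whereas species is read on thin smears, and the day 1 check uses a second sample.
- **330 might count only children who pass every check**, since the day 1 species and density checks are called inclusion criteria. The text does not support this reading. Enrolment is placed before treatment, and the haemoglobin rule expressly removes children after enrolment.
- **A missed second dose may overlap with loss to follow-up.** This is fair for a child who simply does not return. It does not cover the other three routes.
- **Failure risks are to be estimated by Kaplan-Meier on a modified intention-to-treat basis**, so a child lost late still contributes. This is true for the analysis, but the sample-size section states a number of completers, and that number is what does not follow.
- **300 is a resource limit, and no power level or alpha is given**, so no stated threshold is missed. The primary outcome is pharmacokinetic. This stands and limits the weight of the point.

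A reader might infer that the inflation slip by itself makes the trial miss its 22 failures, or that a 5 to 10% exclusion loss is established. Neither is supported. The slip leaves 22.3 failures, and every figure below 297 depends on an assumed rate.

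**Conclusion.** The point holds as a minor inconsistency. On the protocol's own 10%, 330 enrolled gives 297 completers. Because the exclusions after enrolment come on top of that loss, 297 is the most that the plan's rules can be expected to deliver. The 297 rests only on stated figures.

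The shortfall below 297 cannot be sized from the document. Over an assumed 2 to 10% it is about 6 to 30 children and at most about two failures. The power figures rest further on the assumed alpha, sidedness and 15% v 5% split. Nor does this show that more children must be enrolled. Power is below 80% even at 300 under these assumptions, but that is a separate matter and is not caused by the inflation or the exclusions.

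**What to change.** Amend the sample-size section in one of two ways.

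1. Keep 330 as the number enrolled. State that 10% loss to follow-up leaves at most 297 completers, and fewer after the exclusions listed elsewhere in the protocol. Give an assumed exclusion rate, labelled as such, and carry the resulting completers and expected failures into the power sentence (for example, 5% assumed: about 282 completers and 21 failures).
2. Define 330 as the children remaining after the day 0 to 1 and dosing exclusions, and quote 297 completers and 22 failures.

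The first costs a sentence or two and adds no enrolment. The second leaves the target of 330 unchanged but means taking in a few more children to replace those excluded. Neither touches the exclusion rules or clinical management.

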### Risk of dihydroartemisinin-piperaquine (DP)

### DP is an artemisinin-containing fixed-combination drug developed in China. Recent randomized clinical trials in Cambodia, Vietnam, Thailand, Uganda, and Burkina Faso indicate excellent tolerability and high cure rates against multi-drug resistant falciparum malaria. Artemisinin derivatives such as dihydroartemisinin have been used safely in large numbers of patients with uncomplicated or severe malaria. Piperaquine has been used less widely, but it has been a standard antimalarial drug in China since the 1970s. Data from in vitro and animal studies suggest that it is as potent as chloroquine but less toxic. [12, 14] In the first human studies of piperaquine, the main side effects were mild headache, listlessness, nausea, and dizziness. [15]In a study of the safety and efficacy of DP in 106 Cambodian children and adults with uncomplicated malaria, adverse events were uncommon (< 5%), mild, short lived, and difficult to distinguish from symptoms of malaria (anorexia, nausea, vomiting, abdominal pain, diarrhea, and dizziness). [16]In a safety evaluation of DP in 62 Cambodian children and adults with malaria, DP was found to be safe and well tolerated with no evidence of clinically significant postural hypotension, QTc prolongation, or propensity for hypoglycemia.[17] In a clinical trial of DP in 166 Vietnamese patients with uncomplicated malaria, 3% of patients reported minor adverse events, mostly transient nausea, which were self limited and resolved with the abatement of fever.[18] In a dose-optimization clinical trial of DP in 487 children and adults from Thailand with uncomplicated malaria, DP was well tolerated, with a low incidence of mild adverse events, which were mainly upper gastrointestinal and were similar to those reported in other studies.[19] In a clinical trial of DP in 331 children and adults from Thailand with uncomplicated malaria, DP was well tolerated, with a low incidence of mild side effects and no serious adverse events felt to be related to the study drug. [20]In 211 patients treated with DP in Uganda, the drug was well tolerated, and all serious adverse events were judged unrelated to the study drug [21]. In 187 patients treated with DP for malaria in Burkina Faso, the drug was well tolerated, with no serious adverse events (Zongo, et al., submitted). DP is now in routine use in Vietnam with no reports of serious adverse events (although limited resources are available for pharmacovigilance).

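### The power statement names a 3-fold difference in efficacy, which 7.5% failure rules out; read as failure risk, power is about 61-78% at an assumed two-sided 5%

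*Protocol*

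**What the plan says.** The Protocol, under Data collection and management, section 4 (Statistical analysis and sample size), builds up to the power statement in steps:

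- The number of completers: "Available resources will allow us to study 300 patients who complete study follow-up".
- Enrolment: "Estimating a 10% loss to follow-up over 42 days, we will enroll 330 patients".
- The assumed failure risk, from the group's recent study at the same sites: "the unadjusted 42 day risk of treatment failure with DP was 7.5" percent.
- The expected events: "studying 300 patients will identify 22 unadjusted treatment failures".
- The capability claimed: "This sample size will provide the power to identify a 3-fold difference in unadjusted treatment efficacy between the lowest piperaquine level quartile" and all other children.

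No power percentage, significance level, sidedness or test accompanies the claim.

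**The concern.** The sentences leading up to the claim deal with failures, but the claim itself is about efficacy. When 92.5% of children are treated successfully, efficacy cannot be three times higher in one group than in another. This is the Protocol's only statement of what the association analysis can detect, and it describes something that cannot happen.

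Replacing the word is not enough. The sentence says that the sample provides the power without saying how much. A reader will normally take that to mean at least 80% at two-sided 5%, and the Protocol's own inputs do not deliver that for a 3-fold failure risk. The search for links between outcome and pharmacokinetics is the third listed objective, so its stated capability should be right.

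**Working it through.** **Inputs, all from the sample-size section:** 300 completers; overall unadjusted 42-day failure risk 7.5%; lowest quartile v remainder, so 75 v 225; a 3-fold difference. **Assumption, not in the Protocol:** two-sided alpha of 5%, with one-sided 5% as an alternative.

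**1. The Protocol's own event count.** 300 × 0.075 = 22.5, which agrees with the stated 22.

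**2. Can efficacy differ 3-fold?** Let efficacy be x in the lowest quartile and 3x in the remainder. Then 0.25x + 0.75(3x) = 0.925, so x = 0.925/2.5 = 37% and 3x = 111%, which is impossible. The most extreme split puts every failure in the lowest quartile: 22.5/75 = 30% fail there, so efficacy is 70% v 100%, a ratio of 100/70 = 1.43.

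**3. The same statement on failure risk.** Let the risk be p in the remainder and 3p in the lowest quartile. Then 0.25(3p) + 0.75p = 1.5p = 0.075, so p = 5% and 3p = 15%.

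**4. Power for 15% v 5%, 75 v 225, two-sided 5% (pooled normal approximation).**

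- Standard error under no difference: √[0.075 × 0.925 × (1/75 + 1/225)] = 0.0351
- Standard error under the alternative: √[0.15 × 0.85/75 + 0.05 × 0.95/225] = 0.0437
- Power = Φ[(0.10 − 1.96 × 0.0351)/0.0437] = Φ(0.71) = 76.2%

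Other methods with the same inputs:

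| Method | Two-sided 5% | One-sided 5% |
|---|---|---|
| Chi-square, enumerated | 78.1% | 84.0% |
| Pooled normal | 76.2% | 83.3% |
| Arcsine | 73.3% | 82.6% |
| Fisher exact | 72.4% | 77.8% |
| Continuity-corrected | 69.5% | 77.7% |
| Unpooled normal | 62.8% | 74.0% |
| Schoenfeld, hazard ratio 3, 22-23 events | 61-63% | 72-74% |

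No two-sided method reaches 80%. At one-sided 5%, some do and some do not.

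**5. What 300 completers can detect with 80% power (two-sided 5%, overall risk held at 7.5%).** For risk ratio R, the risk in the remainder is 0.075/(0.25R + 0.75).

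- R = 3.2 gives 15.5% v 4.8%: 80.3% pooled, 77.3% Fisher.
- R = 3.35 gives 15.8% v 4.7%: 82.9% pooled, 80.5% Fisher.

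The detectable risk ratio is therefore about 3.2 (pooled) to 3.35 (Fisher). Conversely, 80% power at a risk ratio of exactly 3 would need about 336 completers by the pooled formula, or 388 with continuity correction.

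**6. The alternative reading.** If 7.5% is the risk in the remainder, the comparison is 22.5% v 7.5%, and pooled power is 90.6%. The overall risk is then 0.25 × 22.5% + 0.75 × 7.5% = 11.25%, or 300 × 0.1125 = 33.75 failures. The Protocol states 22.

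**The case against.** **The intended scale is clear.** The neighbouring sentences all concern failures, so the word efficacy can be seen as a slip. That stands, and it is why steps 3 to 5 use failure risk. It does not make the printed sentence correct.

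**No printed percentage is contradicted.** The Protocol gives no power or alpha, and its hypothesis is directional: low piperaquine levels are expected to go with more failures. A one-sided 5% test with the pooled formula gives 83.3%. This stands too. The shortfall is measured against an assumed convention, and a single narrow figure would overstate how well power is known when no test has been named.

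**The gap is small.** On the pooled calculation, 80% is reached at a risk ratio of 3.2, which could be rounded to 3-fold. That is fair for the pooled and Fisher calculations, but less so for the methods that give 61-63%.

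**Stronger readings that the Protocol does not support:**

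- A reader might infer that the size of the trial rests on this sentence. It does not: the same section sets 300 by available resources. Under Study design, section 3 (Study outcome), the primary outcome is pharmacokinetic parameters, and exposure-response work depends on enough recurrences occurring.
- A reader might take the 7.5% to come from the patients mentioned under Risks and discomforts ("In 187 patients treated with DP for malaria in Burkina Faso") and build a range for the failure risk from that number. That passage reports tolerability only and is not tied to the 7.5%. The sample-size section gives no denominator for its figure.
- A reader might expect a null result to be presented as excluding a 3-fold effect. The Protocol sets no rule for interpreting a null result.

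**Conclusion.** The concern holds in two parts of unequal strength.

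- **Certain, with no outside assumption:** the stated 3-fold difference in efficacy cannot occur with 7.5% overall failure. The ceiling on the ratio is about 1.43.
- **Conditional on an assumed two-sided 5%:** for a 3-fold failure risk with the Protocol's inputs, power is about 61-78% depending on the method (76% pooled, 72% Fisher). That is below the conventional 80%, but it is not a contradiction of any stated target. At one-sided 5% the pooled and Fisher figures are 83% and 78%.

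The 22.5% v 7.5% reading does not rescue the claim, because it conflicts with the stated number of failures.

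Severity is moderate. The statement describes the capability of a lower-ranked, conditional analysis in a sample fixed by resources, and the primary pharmacokinetic outcome is untouched.

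**What to change.** In the Protocol's sample-size section, replace efficacy with the risk of unadjusted treatment failure, name the test, alpha and sidedness, and give the power as a number. For example:

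*With 300 completers and 7.5% failing overall, power at two-sided 5% to detect a failure risk of 15% in the lowest piperaquine quartile v 5% in the remainder (risk ratio 3) is about 76% (pooled normal approximation) or 72% (Fisher exact). The risk ratio detectable with 80% power is about 3.2 to 3.35.*

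Once the test is chosen, keep only its figure. If the sponsor intends a one-sided test, say so and quote the matching power. If 22.5% v 7.5% was intended, the expected number of failures must change to about 34 and the overall risk to 11.25%, with a reason for departing from the 7.5% observed.

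The cost is one rewritten sentence and a slightly less favourable stated capability. No extra patients, visits or assays are needed.
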